#### **6.5 Fasting**

Subjects will be asked to fast on D0, W 4, W8 and W12 visits. This will usually be from midnight the preceding evening. However, if dosing is not scheduled to take place before midday on D0, W4, W8 or W12, a light breakfast is allowed. Subjects must fast at least 4 hours before the pre-dosing blood draw.

## **7 STUDY PRODUCTS**

### **7.1 Randomisation process**

Potential subjects who provide written informed consent will be sequentially assigned a Screening Number prefixed by “S” (S001- ) and subjects who meet the inclusion/exclusion criteria and are to be randomised will be assigned a Subject Number 001 to 027 sequentially. A randomisation scheme will be prepared in advance by the study statistician using a computer generated system according to relevant SOPs. The scheme will have the property that within each dose cohort, the initial sentinel cohort of 2 clade C subjects will be randomised 1:1 to receive active treatment or placebo, the next 3 clade C subjects will be randomised in a 2 (active):1 (placebo) ratio, and the remaining 4 subjects (who may be of any clade) will be randomised in a 3:1 ratio.

### **7.2 Blinding**

The study will be conducted double-blind. Study subjects, investigators and monitors will be blind to the administration of active or placebo to subjects. The study pharmacist or delegate will not be blinded during the study and will have access to the randomisation code. The treatment procedure will require an unblinded pharmacist for the preparation and delivery of the study materials. In order to maintain the blind, the pharmacist will not divulge the treatment allocations to any other study or sponsor staff. Treatment will be labelled and presented in a manner that does not break the blind.

### **7.3 Treatment Allocation**

The pharmacist will prepare the treatment corresponding to the Subject Number in the randomisation scheme, stratifying according to HIV clade. The first two subjects must be clade C. A period of at least 2 days must elapse between the start of treatment of sentinel subjects and the start of treatment for remaining subjects in the same cohort. The pharmacist will record the name of the subject and the randomisation date against the Subject Number on the randomisation scheme. This entry must be signed by the pharmacist.

### **7.4 Method of Unblinding**

#### **7.4.1 Medical emergency**

As the study is blinded, the clinical site, the laboratories, the Contract Research Organisation (CRO) or MDL will not have access to the open randomisation scheme. However, pharmacy will hold the open randomisation scheme and sealed code break envelopes will be held by the clinical site, medical monitor and MDL. In the event of a medical emergency requiring breaking of the blind, the Investigator must contact MDL or the Medical Monitor prior to doing so. The breaking of the blind will only be sanctioned where knowledge of the study medication treatment will affect subject management.

If the code is broken, the envelope must be signed and dated by the individual who broke the code, and the Code Break Log completed (and information entered into the subject's source documents and CRF), explaining the reason and date that it was opened, identity of the person who authorised the code break, and documenting the identity of the study treatment allocated to the subject. The Code Break Log must be signed and dated and countersigned by the Investigator.

#### **7.4.2 End of study**

The randomisation code will be broken by the study statistician once data entry has been completed, the database locked, the per-protocol population for analysis established and the Statistical Analysis Plan (SAP) finalised and approved. MDL will provide written permission to the study statistician prior to the breaking of the randomisation code.

## 7.5 Investigational medicinal products

### 7.5.1 Formulation

The active IMP (Opal-HIV-Gag(c)) contains 120 peptides (15 amino acids in length overlapping the preceding peptide by 11 amino acids) spanning the HIV-1 clade C Gag protein. The peptides were synthesised and lyophilised by CS Bio Inc. (USA) according to US FDA standards of cGMP as defined by United States 21 Code of Federal Regulations.

To formulate the Opal-HIV-Gag(c), individual peptides were reconstituted and pooled in equal amounts by weight. The pooled peptides were filled into vials (at 60 mg/vial), lyophilised to produce a dry powder and sterilised by terminal gamma irradiation. The final product release specifications are listed in the IB. The material for clinical administration will be released by a qualified person according to the regulations for release of IMP manufactured outside the EU for use in European trials.

The comparator placebo material will consist of the diluent only delivered using the same method of administration. The diluent for the active and the placebo is DMSO USP/ Ph Eur. To minimise the risk of toxicity associated with DMSO, the overall concentration of the DMSO will be 4% volume per volume (v/v). Side effects are reported more commonly in stem cell transplantation where 10% DMSO v/v is used in standard procedures and reinfused. The re-infusion will also be a slow push or controlled infusion by infusion pump (not more than 5 mL/min), to reduce the risk of vasospasm or toxicity. Subjects will be monitored and history of allergy to DMSO will be an exclusion criterion to participation in the study.

### 7.5.2 Supply, packaging and labelling, storage and handling

The Opal-HIV-Gag(c) must be stored in a secure area with access limited to the unblinded pharmacist and authorised staff.

The vials and outer packaging will be stored at -20°C in a controlled and monitored freezer (range -25°C to -15°C).

At a minimum, the immediate packaging will include the following information:

- sponsor name
- protocol number Opal-HIV-1001
- product name/drug code
- dose/product strength
- route of administration
- lot number
- directions for use
- expiry date or retest date (on outer packaging)
- 'For Clinical Trial Use Only'

Any specific cautionary statements will be included according to local law.

Opal-HIV-Gag(c) will be administered by mixing with blood that has been removed and processed via a Sepax S-100 device (CE marked) and single use kit. Opal-HIV-Gag(c) will be provided to Pharmacy and single use kits will be provided to the site. The single use kits must be stored protected from light and in accordance with the manufacturer's specifications. Kits must not be used if they have exceeded their expiry date or if the sterility label is compromised on the packaging (refer to Study Reference Manual).

DMSO Ph Eur/USP is provided as commercially available supply and will be labelled and stored in accordance with the manufacturer's specifications.

### 7.5.3 Dosage and administration of investigational medicinal product

Only subjects enrolled in the study may receive Opal-HIV-Gag(c) or matching placebo. Subjects will receive Opal-HIV-Gag(c) or matching placebo at St Stephen's Centre.

#### 7.5.3.1 Dose of investigational medicinal product

The dosage calculations at each dose level for each visit (W0, 4, 8 and 12) are provided in Table 3 below. Further details of dose and reconstitution are listed in 7.5.3.2 and the Study Reference Manual.

**Table 3: Dose of investigational medicinal product in 20 mL WBC-enriched blood component**

| Dose cohort | Dose per peptide            | Total amount of Opal-HIV-Gag(c) | Volume DMSO as diluent added to reconstitute | Final volume of IMP drawn into syringe and administered# |
|-------------|-----------------------------|---------------------------------|----------------------------------------------|----------------------------------------------------------|
| 1*          | 5 microgram (µg)/peptide/mL | 12 mg                           | 4 mL                                         | 800 µL                                                   |
| 2*          | 10 µg/peptide/mL            | 24 mg                           | 2 mL                                         | 800 µL                                                   |
| 3*          | 20 µg/peptide/mL            | 48 mg                           | 1 mL                                         | 800 µL                                                   |

\* Refers to active IMP administration. Placebo recipients for all dose cohorts will be administered 800 µL of DMSO diluent.

# The administered volume of IMP for all Opal-HIV-Gag(c) and placebo is 800 µL, which will constitute a total of 4% v/v of DMSO added to the 20 mL WBC enriched cells.

#### 7.5.3.2 Administration of investigational medicinal product

The following activities are required for preparation and administration of the IMP, in accordance with the randomisation scheme (please refer to the Study Reference Manual for further details):

##### Pharmacy Procedure

Prepare the IMP for one subject at a time. The preparation of the IMP must be conducted by pharmacy personnel experienced in the use of aseptic techniques within an appropriate area for preparation of sterile products (such as a pharmacy isolator). The maximum time from drawing the Opal-HIV-Gag(c) dissolved in DMSO Ph Eur/USP or DMSO Ph Eur/USP placebo into the dosing syringe to addition of the IMP to the WBC component should not exceed 3 hours. The IMP in the dosing syringe is to be kept at room temperature (within an insulated "cool box") prior to addition to the WBC component.

##### Preparation of placebo dose:

1. Within the area appropriate for preparation of sterile products and using aseptic technique:
  - a. Swab the DMSO Ph Eur/USP lid with alcohol
  - b. Withdraw 800 µL from the vial of DMSO Ph Eur/USP with a sterile 1 mL polypropylene syringe and needle
  - c. Remove and discard the needle and immediately attach a sterile capped needle to the syringe
  - d. On the syringe label, complete the subject number, and attach label to the syringe
2. Place the syringe in an insulated "cool box" at room temperature for transfer to the clinical site
3. Record the lot number of the DMSO Ph Eur/USP and discard any remaining DMSO Ph Eur/USP
4. Contact the clinical site personnel for collection of IMP.

##### Preparation of Opal-HIV-Gag(c) dose:

1. Remove a vial of Opal-HIV-Gag(c) from storage at -20°C and thaw at room temperature for 30 minutes
2. Within the area appropriate for preparation of sterile products and using aseptic technique:
  - a. Swab the DMSO Ph Eur/USP lid with alcohol

- b. According to the table below, withdraw the required volume of DMSO Ph Eur/USP from the vial using a sterile 5mL polypropylene syringe with a needle

| Dose cohort | Volume of DMSO Ph Eur/USP for reconstitution |
|-------------|----------------------------------------------|
| 1           | 4 mL                                         |
| 2           | 2 mL                                         |
| 3           | 1 mL                                         |

- i. Swab the Opal-HIV-Gag(c) vial lid with alcohol
  - ii. Inject the required volume of DMSO Ph Eur/USP into the vial of Opal-HIV-Gag(c), discard needle and syringe and swirl the vial to reconstitute material, checking it is dissolved fully
  - iii. Using a sterile 1 mL polypropylene syringe with a needle, draw 800 µL of Opal-HIV-Gag(c) in DMSO Ph Eur/USP solution into the syringe
  - iv. Remove and discard the needle and immediately attach a sterile capped needle
  - v. On the syringe label, complete the subject number according to the randomisation code, and attach label to the syringe.
- c. Place the syringe with capped needle in a insulated “cool box” at room temperature for transfer to the clinical site
3. Record the lot numbers of the Opal-HIV-Gag(c) and DMSO Ph Eur/USP and discard any remaining DMSO Ph Eur/USP
  4. Contact the clinical site personnel for collection of IMP.

### Clinic Procedure

Standard clinical procedures are to be used throughout the administration of the IMP unless otherwise stated. The IMP must not be directly injected into the subject. The time between the addition of the IMP to the WBC collection bag (Genesis PediPak®, USA) and initiating re-infusion must not exceed 2 hours. The time for infusion must not be less than 5 minutes and should not exceed 1 hour.

#### IMP storage at the clinic:

1. The IMP should be retained at room temperature in the insulated “cool box” upon arrival at the clinic until required

#### Blood collection for IMP administration:

2. A total of 120 mL of whole blood is collected into the whole blood collection bag (Pall Medical Cord Blood Collection System 791-01U, USA), with the volume determined using a CM350 blood collection monitor (Genesis®, USA)

#### Blood separation kit modification and blood separation:

3. Using the sterile connection device (Terumo TSCD-II Sterile Tube Welder®), attach a sterile single use blood separation kit (Biosafe, Switzerland) to a sterile WBC collection bag (Genesis PediPak®, USA) and the whole blood collection bag  
Note: The WBC collection bag collects the separated WBC component
4. Separate the blood into three components (plasma, RBC and WBC) using the Sepax® S-100 cell separation device and the “Generic Volume Reduction Protocol”
5. Remove the bag containing the WBC component (there should be approximately 20 mL in the Genesis PediPak®) from the blood separation kit) by heat sealing using a rapid seal SE700 hand tubesealer™ (Genesis, USA) at 3 points of the tubing and cutting between the seals
6. Discard the kit and remaining blood components (plasma and RBC) appropriately
7. Use the sterile connection device to attach a sterile AK-100 sample line to the WBC collection bag and collect 0.5 mL of the WBC component. Remove the sample line by heat sealing using a rapid seal SE700 hand tubesealer™ (Genesis, USA) at 3 points of the tubing and cutting between the seals.

Incubation of IMP and re-infusion:

8. Remove the syringe and needle containing the IMP from the insulated “cool box”
9. Swab the non-latex injection site with alcohol
10. Inject the IMP into the WBC collection bag through the non-latex injection site on the bag
11. Mix the IMP and WBC component by gentle inversion of the bag 5 times and place into the incubating rocking platform shaker (VWR Signature™ USA) for 1 hour at 37°C
12. Attach an infusion giving set for blood into the sterile access port on the WBC collection bag
13. Using an infusion pump with the giving set, administer the infusion intravenously over a period of time not less than 5 minutes
14. Flush with approximately 50 mL of sterile saline
15. Remove and discard the infusion giving set.

**7.5.4 Dispensing and accountability**

The pharmacist or delegate will be responsible for maintaining accurate records for all study medications dispensed and returned. The inventory must be available for inspection by the study monitor. Study product supplies, including partially used or empty vials, must be accounted for by the study monitor and returned to the drug repository for destruction at the end of the study.

When requested in writing by the sponsor, unused study medication supplies may be destroyed by the pharmacy according to their SOPs provided such disposition can be performed safely. Records shall be maintained by the Investigator for any alternate disposition of the study medication. These records must show the identification and quantity of each unit disposed of, the method of destruction (taking into account the requirements of local law) and the person who disposed of the test substance. Such records shall be submitted to the sponsor.

## **8 CONCOMITANT MEDICATIONS AND TREATMENTS**

At each study visit or contact, the Investigator should question the subject or their legal representative about any medication taken. Concomitant therapies should be brought to the attention of the Investigator. Any such medications will be recorded on the CRF. Any changes in doses or introduction of new medications during the course of the study will also be recorded.

### **8.1 Special Dietary Requirements**

There are no special dietary requirements.

### **8.2 Concomitant Medications / Treatments Not Permitted**

#### **8.2.1 Prior to study entry**

Refer to Exclusion Criteria in Section 5.3.

#### **8.2.2 During the study dosing period**

Throughout the study medication dosing period, subjects may not receive any of the following concomitant medications:

- immunomodulators, immunoglobulins and other blood products, cytotoxic chemotherapy or the any use of experimental agents are not permitted
- live attenuated vaccines may not be administered within 60 days of entering and throughout the duration of the study
- whole killed/toxoid (influenza, pneumococcal, tetanus) or sub-unit vaccines (hepatitis B) should not be given during the vaccination period of the study or in the 30 days following the last vaccination unless medically indicated.

All concurrent medications, including vitamin supplements and herbal remedies, must be recorded in the appropriate section of the CRF.

Every effort should be made to keep chronic concurrent medications stable throughout the study period.

## 9 ADVERSE EVENTS AND TOXICITY MANAGEMENT

### 9.1 Safety Parameters

Safety parameters will include AEs (see Section 9.2 ), vital signs (see Section 6.3.1), clinical laboratory tests (see Section 6.3.3), physical examinations (see Section 6.3.1 ) and ECG's (see Section 6.3.2).

### 9.2 Adverse Events

An AE is any untoward medical occurrence in a subject or clinical investigation subject administered an IMP (i.e. whether it is the experimental product or the placebo) and which does not necessarily have a causal relationship with the IMP. An AE can therefore be any unfavourable and unintended sign, symptom, or disease temporally associated with the use of a medicinal product, whether or not considered related to the medicinal product. Pre-existing events, which increase in frequency or severity or change in nature during or as a consequence of use of a drug in human clinical trials, will also be considered as AEs. AEs may also include pre- or post-treatment complications that occur as a result of protocol-mandated procedures (e.g. invasive procedures such as biopsies).

Any medical condition or clinically significant laboratory abnormality with an onset date before the first date of study product administration is considered to be pre-existing, and should be documented in the CRF.

Any AE (i.e. a new event or an exacerbation of a pre-existing condition) with an onset date after study product administration up to the last day on study (including the follow-up, off study medication period of the study), should be recorded as an AE on the appropriate CRF page(s).

An AE **does not** include:

- medical or surgical procedures (e.g. surgery, endoscopy, tooth extraction, transfusion); the condition that leads to the procedure is an AE
- pre-existing diseases or conditions present or detected prior to start of study product administration that do not worsen
- situations where an untoward medical occurrence has not occurred (eg. hospitalisation for elective surgery, social and/or convenience admissions)
- overdose of either study product or concomitant medication without any signs or symptoms unless the subject is hospitalised for observation.

#### 9.2.1 Assessment of Adverse Events

All AEs will be assessed by the Investigator and recorded on the appropriate CRF page, including the date of onset and resolution, severity, relationship to study product, outcome, action taken with study medication, and seriousness.

Severity should be recorded and graded according to the AIDS Clinical Trial Group (ACTG) grading scale (see Appendix A) or, if there are no specific toxicity grades for the parameter, the grading in Table 4 used.

**Table 4: Grading Scale where AIDS Clinical Trial Group Toxicity Grades Do Not Apply**

| Grade   | Severity         | Definition                                                        |
|---------|------------------|-------------------------------------------------------------------|
| Grade 1 | Mild             | Aware of sign or symptom, but easily tolerated                    |
| Grade 2 | Moderate         | Discomfort enough to cause interference with usual activities     |
| Grade 3 | Severe           | Incapacitating with inability to work or perform usual activities |
| Grade 4 | Life-threatening | Participant is at immediate risk of death                         |

The relationship to study product therapy should be assessed using the following definitions:

- Unrelated:** AE is clearly due to extraneous causes (e.g. underlying disease, environment)
- Unlikely:** The temporal association between the AE and IMP is such that IMP is not likely to have any reasonable association with the AE
- Possible:** The AE could have been produced by the subject's clinical state or IMP
- Probable:** The AE follows a reasonable temporal sequence from the time of IMP administration, abates upon discontinuation of the IMP and cannot be reasonably explained by the known characteristics of the subjects clinical state
- Definite:** The AE follows a reasonable temporal sequence from the time of IMP administration, abates upon discontinuation of the IMP and/or reappears when IMP is re-introduced

These criteria in addition to good clinical judgment should be used as a guide for determining the causal assessment. If it is felt that the event is not related to IMP, then an alternative explanation should be provided.

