## 4 STUDY DESIGN

### 4.1 Study Design

This is a phase I, randomised, double-blind, single-centre, sequential dose-escalation, placebo-controlled study of the safety and immunogenicity of Opal-HIV-Gag(c) in HIV-1 positive subjects.

Approximately 27 subjects will be enrolled and followed for 24 weeks on both an inpatient and outpatient basis. Subjects will be treated on 4 occasions over 12 weeks. After completion of treatment at W12, subjects will be followed for 12 weeks for safety and immunogenicity assessments.

Each dose group will be enrolled sequentially, with a sentinel group for each cohort. Satisfactory safety data (from 2 immunisations and 1 week follow up) from each cohort will permit recruitment to the next dose group (see Figure 1). A minimum number of 7 subjects completing the dose level for each dose cohort will be required for a DSMB review for dose escalation. A total of 7 subjects will ensure that at least 4 subjects have received administration of Opal-HIV-Gag(c).

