### 4.2 Dosing Regimens

After screening, subjects will be randomised to the following treatment regimens, starting with the lowest dose (1) and escalating to the highest dose (3):

1. 12 mg Opal-HIV-Gag(c) (n=6) or placebo (n=3)
2. 24 mg Opal-HIV-Gag(c) (n=6) or placebo (n=3)
3. 48 mg Opal-HIV-Gag(c) (n=6) or placebo (n=3)

Within each dose cohort, there will be an initial sentinel cohort of 2 subjects who will be randomised sequentially on a 1:1 basis to receive Opal-HIV-Gag(c) or placebo. The remainder of subjects will be randomised no sooner than 2 days after randomisation of the sentinel subjects.

Subjects will be stratified based on clade of infection. There will be a minimum of 5 clade C subjects per cohort, with the remaining 4 subjects being any clade. The 2 sentinel subjects in each cohort must

be clade C. After the sentinel dosing, the next 3 clade C subjects will be randomised 2:1, and the remaining 4 subjects (of any clade) randomised 3:1.

All subjects will receive a total of 4 immunisations; at D0, 28 (W4), 56 (W8) and 84 (W12). Immunogenicity will be assessed at D0, 70 (W10), 84 (W12), 91 (W13), 98 (W14) and 112 (W16) and all subjects will be followed until W24.

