## 10 DATA SAFETY MONITORING BOARD REVIEW

The Sponsor has convened a DSMB that is charged with the review of this study. The DSMB review will occur as soon as practical after the W4 dose administration of IMP is complete for each cohort and will include all available safety data.

Each DSMB meeting will have an open session and an optional closed session. Open session review materials will be blinded and include aggregate data on study accrual, baseline characteristics and general study progress, and will be made available to the DSMB, Sponsor representatives, and invited guests (e.g. participating Investigators) to facilitate a general discussion of study progress. Attendance at the closed session will be restricted to DSMB members and those individuals who were directly involved in the preparation of the review materials. The DSMB will review available safety results of the trial and logistical issues such as accrual, retention, quality of clinical and laboratory data, and safety and implications of results of external studies. Unblinding envelopes will be made available to the DSMB should unblinding be requested.

The DSMB will make its recommendation to the Sponsor about dose escalation, halting or termination of the clinical trial. At each meeting the DSMB will review all available safety data and the DSMB will recommend to the Sponsor to:

- proceed with dose escalation
- pause enrolment pending either resolution of specific issues or amendment of the protocol as specified
- pause enrolment and all scheduled trial administrations pending either resolution of specific issues or amendment of the protocol as specified
- terminate the study

The DSMB, following a meeting to review the data, may recommend to the Sponsor and Principal Investigator not to permit further dose escalation if any of the following conditions are met:

- a subject experiences a SAE regarded as “probably” or “definitely” related to Opal-HIV-Gag(c) (i.e unblinded review of the event)
- any three subjects experience a similar severe adverse event (with a toxicity of at least grade 3) which is “probably” or “definitely” related to Opal-HIV-Gag(c) (i.e. unblinded review of the events)
- the Principal Investigator, DSMB and/or the Sponsor feel that consideration by the DSMB of a full interim safety summary is warranted following detection of a pattern of repeated or unresolved clinical AEs or laboratory abnormalities.

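### Read literally, Definite in Section 9.2.1 needs no exclusion of other causes and contains every Probable event, while an unexplained irreversible event that does not recur reaches only Possible

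*Protocol*

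**What the plan says.** The relationship definitions stand below Table 4 in Section 9.2.1 of the protocol. The three upper categories are:

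- Possible: "The AE could have been produced by the subject's clinical state or IMP".
- Probable: the timing fits, and the event "abates upon discontinuation of the IMP and cannot be reasonably explained by the known characteristics of the subjects clinical state".
- Definite: the timing fits, and the event "abates upon discontinuation of the IMP and/or reappears when IMP is re-introduced". There is no clause on other explanations.

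The section limits its own force: "These criteria in addition to good clinical judgment should be used as a guide for determining the causal assessment".

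Section 10 lists three conditions, any one of which allows the DSMB to recommend against further escalation. The first applies when "a subject experiences a SAE regarded as" probably or definitely related to the product. The second applies when "any three subjects experience a similar severe adverse event (with a toxicity of at least grade 3) which is" probably or definitely related. Both call for unblinded review. The third concerns a pattern of repeated or unresolved events and uses no causality category.

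On the data behind escalation, Section 4.1 says: "Satisfactory safety data (from 2 immunisations and 1 week follow up) from each cohort will permit recruitment to the next dose group". Section 4.2 sets four doses, at weeks 0, 4, 8 and 12. Section 12.6.4.1 plans to show adverse events by relationship to treatment.

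**The concern.** A causality scale should become more demanding as it rises. Here the top category drops the exclusion of other causes that the category below it requires, and the words and/or let abatement alone satisfy it. Both upper categories also depend on the event going away or coming back. A fatal or permanent event that happens once can do neither, so the wording caps it at Possible even when nothing else explains it.

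Safety is the primary objective of this first-in-human study, and two of the three no-escalation conditions use the words probably and definitely, which the protocol defines only in Section 9.2.1. At stake are the order of the investigator's ratings, the relationship tables built from them, and whether an unexplained irreversible event counts under those two conditions.

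**Working it through.** The plan gives no figure on this point, so the check is one of logic. The inputs are the three definitions in Section 9.2.1, the conditions in Section 10, the dose schedule in Sections 4.1 and 4.2, and Table 5.

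**Step 1: formal reading.** Suppose the timing fits. Let A = abates on discontinuation, R = reappears on re-introduction, E = explained by the subject's clinical state. Then Probable = A and not E, and Definite = A or R. The 2 × 2 × 2 = 8 combinations are:

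| A | R | E | Probable | Definite |
|---|---|---|---|---|
| yes | yes | no | yes | yes |
| yes | no | no | yes | yes |
| no | yes | no | no | yes |
| yes | yes | yes | no | yes |
| yes | no | yes | no | yes |
| no | yes | yes | no | yes |
| no | no | no | no | no |
| no | no | yes | no | no |

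Both Probable rows are also Definite. Three of the six Definite rows have another explanation. The seventh row, unexplained with neither abatement nor recurrence, reaches neither category, so Possible is the highest it meets. These rows are logical cases without weights; they do not say how often each would occur.

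**Step 2: other readings.** If reappearance is taken to suffice without the timing clause, every Probable case is still Definite. Only if and/or is read as plain and does a Probable case fall outside Definite (the second row), and that is not what the text says. The seventh row reaches neither category under any of the three readings.

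**Step 3: the recurrence route.** Four doses give 4 − 1 = 3 re-introductions. The escalation data require two doses, so 2 − 1 = 1 re-introduction, and an event that first appears after the week 4 dose has none within that minimum. This is a floor: Section 10 has the DSMB look at whatever safety data exist, and subjects enrolled early may have had later doses. Table 5 narrows the route for grade 3 and 4 events. Where a clinical event, or a clinically significant laboratory event, is of unknown or at least possible relation, dosing stops for good, apart from transient grade 3 clinical events expected of a vaccine. Without a further dose there is nothing to recur after.

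**Step 4: link to Section 10.** The seventh-row event, rated literally, does not meet the first two conditions. The fourth to sixth rows, which have another explanation, can.

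**Step 5: test of the replacement.** Take Definite = not E and R, and Probable = not E and (A or irreversible), recording the highest category met. Unexplained events split into 4 reversible cases (A yes/no, R yes/no) and 2 irreversible ones (A no, R yes/no), 6 in all.

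- Current wording: 3 reversible + 1 irreversible = 4 reach Probable or Definite.
- Replacement: Definite 2 + 1 = 3, Probable 1 + 1 = 2, together 5. All 4 stay, and the irreversible non-recurring case joins as Probable. A reversible event that has neither abated nor recurred stays at Possible.
- Explained events: 4 of 6 are Definite under the current wording and 0 under the replacement.

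**The case against.** The strongest reply is that nobody is told to apply the scale as formal logic. Section 9.2.1 calls the criteria a guide to be used with clinical judgment, so an investigator facing an unexplained death is not bound to Possible. Section 10 does not cite Section 9.2.1, and its first two conditions specify unblinded review, which points to a judgment beyond the blinded rating.

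The protocol also has other routes that do not need a rating above Possible. The DSMB can recommend a pause or termination on its whole review. The third condition covers unresolved events where they form a pattern. The halting rules in Section 10 rest on the Principal Investigator's opinion, and one of them can be triggered by a single serious or severe event. Table 5 stops a subject's dosing at possible relatedness, and Section 9.3.2.2 bases regulatory reporting on a possible causal relationship. The overlap of Probable and Definite changes no escalation decision, because Section 10 treats the two alike, and rating explained events too high errs toward caution.

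All of this stands and limits the consequence. It does not make the definitions right: the freedom to override a definition is no reason to keep one that ranks an unexplained irreversible event below an explained one that abates.

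A reader might infer that escalation would go ahead after an unexplained fatal event. The documents do not support that. The conditions say when the DSMB may advise against escalation, not that it may do so only then, and the halting rule for a single event remains. A reader might also take the case counts as a rate of misrating. They are unweighted and carry no such information. Nor do the probabilities and intervals in Section 12.2 change, since that section does not tie its signal to Probable or Definite.

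**Conclusion.** The point holds as a minor defect of stated wording. Literally read, Definite contains every Probable event and admits events with another explanation, while an unexplained irreversible event without recurrence stops at Possible and need not meet the first two no-escalation conditions.

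Its size is qualitative: two of three conditions use the affected terms, and the relationship tables inherit the ratings. No probability, power or sample size is affected. The conclusion assumes that and/or means what it ordinarily means, that probably and definitely in Section 10 carry their Section 9.2.1 sense, and that ratings follow the text. Where clinical judgment overrides the text, the effect shrinks or disappears. The definition is an instruction to investigators fixed in the protocol, so a later analysis plan would not correct ratings already made under it.

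**What to change.** Reword the two upper categories in Section 9.2.1 and state that the highest category met is recorded:

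- **Definite:** timing fits; the exclusion clause now in Probable also applies; and the event reappears on re-introduction, or there is equivalent evidence, whether or not the product was discontinued in between.
- **Probable:** timing fits; the existing exclusion clause applies; and the event abates after dosing or discontinuation. Abatement is waived where the event is irreversible or abatement cannot be assessed.

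Definite should not also demand abatement on discontinuation. With single infusions four weeks apart, an unexplained reaction may resolve and return at the next infusion while dosing continues; that event is Definite now and should stay so.

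The cost is protocol and CRF-guideline wording plus a re-check of adverse events already rated. The design, sample size and planned summaries stay as they are.
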